### Quantitative and qualitative outcomes

Quantitative assessments will be conducted by researchers at the following time points: T0 = baseline preintervention, T1 = at month three when the intervention has finished (post-intervention), T2 = at month twelve (9-month follow-up) and T3= at month 24 (21-month follow-up) (Table 3 shows the SPIRIT table). All researchers in charge of conducting the assessments will take a standardized training session.

**Table 3 Tab3:**
[figure not shown]
Study timeline

Primary outcomes include (i) PA drop-out ratio; (ii) PA levels; (iii) metabolic and health outcomes (HbA1c, blood pressure, waist circumference and BMI); and (iv) quality of life (SF-12) (see Table 4).

**Table 4 Tab4:** Overview of outcomes, outcome measures, instruments and assessment time points

Outcomes	Outcome measures	Instrument/who measures	Assessment time point
Personal information	Age, gender, civil status, living arrangement, educational background, medical conditions, smoking and alcohol habits.	Primary care records/self-report	T0
Primary clinical trial outcomes			
●Physical activity	Daily counts per minute and intensity of exercise, and daily step counts.	ActivPal®/research team	T0, T1, T2, T3
●Physical activity drop-out ratio	Less of 80% of attendance during the intervention or auto-reported drop out after intervention (yes/no)	Excel/research team	T0, T1, T2, T3
●Quality of life	Physical function, physic role, corporal pain, general health, vitality, social function, emotional role and mental health	SF-12 questionnaire/research team	T0, T1, T2, T3
●Blood pressure	Systolic and diastolic blood pressure; heart rate	OMRON M6 comfort/nurse	T0, T1, T2, T3
●Blood glucose levels (last 3 months)	HbA1c	CATSALUT Dataset	T0, T1, T2, T3
●Anthropometry	Waist circumference and BMI	Measuring tape and coefficient between weight and height/nurse	T0, T1, T2, T3
Secondary clinical trial outcomes			
●Socioeconomic status	Job, education and income	Job and education level and individual and family annual income/research team	T0
●Social network index	Number of social interactions with family friends or mates	Berkman et al. [47] questionnaire with adaptations [48]/research team	T0
●Demographic and background information	Sex, gender, age, ethnic origin, marital and family status or obligations and medication	Self-report information/nurse	T0, T1, T2, T3 (only apply times for medication)
Primary qualitative study outcomes			
●HCP and T2DM perspective on the intervention	Perceptions and experience to examine the feasibility about the intervention and applicability to everyday life	Focus groups /research team	T1

Assessment time points: T0 = baseline pre-intervention, T1 = at month three of intervention, T2 = at month 12 (9 months after the end of the intervention), T3 = at month 24 (21 months after the end of the intervention). *HCP*, health care professionals; *T2DM*, type 2 diabetes mellitus

Demographic outcomes include (v) socioeconomic status and social network index and (vi) demographic and background information that will include sex, gender, age, ethnic origin, marital and family status or obligations and medication (see Table 4).

### PA drop-out ratio

During the intervention, dropout will be considered as less than 85% attendance of scheduled sessions [50].

After the intervention, PA dropout will be measured by asking the participants if they continue to undertake any kind of PA in their daily life. The answer will be registered as yes or no, and it will be noted what kind of PA is done. Participants will be asked once a month until the 21-month post-intervention follow-up through telephone calls and messages. In addition, the SBPAAT screening tool will be used to register whether participants are active or inactive at the follow-ups (*T* = 1, 2 and 3).

### PA assessment

MVPA, light intensity PA (LIPA), standing, total sitting time and sitting bouts will be assessed by the activPAL3™ micro (PAL Technologies Ltd., Glasgow, UK), weighing 9g and measuring 25 × 45 × 5mm [51, 52]. The activPAL^TM^ will be placed in a small flexible nitrile sleeve to waterproof the device and will be attached to the participants’ right thigh using a transparent film (10 × 10cm of hypoallergenic Tegaderm^TM^ Foam Adhesive Dressing). Participants will be instructed to wear the device for 24 h per day during a 7-day period. The recording time will begin at 12am for all participants. Participants will be asked to go to the CAP facilities to fit the activePAL^TM^. A research team member will fit the activPAL^TM^ on the participants’ thighs and will provide them with two additional dressings in case reattachment is required (instructions on how to change the dressings will be explained). Participants will have a field diary to note down if there is any problem with the activePAL^TM^, and to note the time they go to bed and wake up.

The protocol that will be used for data collection and analysis is described in detail elsewhere [53]. Briefly, data will be included in the analyses of the participants who provide a minimum of 4 valid days of recording (including one weekend day) [54]. Valid days will be defined as a day with ≤4h of non-wear time during identified walking hours. Non-wear time is defined as a period with ≥60min of consecutive zero activity counts. Data will be analysed using activPAL^TM^ Professional Software^TM^ (version 7.2.32) and further processes using Microsoft Excel 2010 (Redmond, WA, USA) and METLAB (MathWorks®, Natick, MA, USA).

### Quality of life

Quality of life will be measured using the SF-12 questionnaire (Spanish version) [56]. This questionnaire assesses the quality of life related to health and has 12 items that assess eight dimensions: physical function, physical role, corporal pain, general health, vitality, social function, emotional role and mental health. The SF-12 will be administered by nurses and questions related to it will be answered. Answers follow a Likert scale format and the final score ranges between 0 and 100, where a higher score means a higher quality of life related to health. Patients will complete the SF-12 questionnaire before and after the intervention, and 21 months after intervention.

### Socioeconomic status and social network index

Socioeconomic status will be assessed by occupation, education level and annual income [54]. Occupation will be assessed as a categoric variable (job, no job, retired); education level will be assessed by taking into consideration the highest educational qualification (e.g. degree); and annual income will be assessed [54].

The social network index will be assessed using the adapted Berkman et al. questionnaire [57] on the number of interactions with family, friends, workmates, neighbourhood groups or social groups (e.g. sport clubs).

Social network and socioeconomic status will be recorded by nurses at the beginning of the study during medical consultations and after the intervention at 24 months (21 months after the intervention).

### Patients’ intake of medication

Participants will be asked to agree to use their clinical history to register this outcome in the written informed consent. The same nurses in charge of the caption and randomization of participants will be in charge of recording patients’ intake of medication.

### Patient and HCP experience

Focus groups will be conducted by the research team at T1. The qualitative study will explore the following: (i) HCP opinion regarding the applicability of SENWI in the Spanish healthcare system and (ii) T2DM patients’ perceptions and experience to examine the feasibility of PA adherence in the SENWI protocol. We will include (i) HCPs that participate in the study to deliver the SENWI protocol, (ii) patients with T2DM in the SENWI group that finish the protocol and (iii) patients with T2DM in the SENWI group that did not finish the protocol.

## Data collection and management

All assessments and collection of outcomes will be conducted at the CAP facilities. Nurses will collect all data except activePAL^TM^ and qualitative data. Qualitative data will be collected by the research members ([name] and [name]) at the end of the intervention (*T* = 1). Focus groups for qualitative data will be delivered face-to-face by two research staff members ([name] to undertake the focus group and [name] to take notes), tape-recorded and transcribed verbatim. Overall data management will be done by the research members’ staff at the University of Vic-Central University of Catalonia.

The number of participants that decline to participate in the study and those withdrawing during the course of the study will be tabulated by reason for not participating, and by reason for withdrawing (voluntarily given). Confidentiality of personal information about potential and enrolled participants will be protected using codification (number of participants; number of groups; number of outcome assessments) before, during and after the trial by the principal investigator ([name]) at a University of Vic-University of Central Catalonia computer server.

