**Table Tabb:** 

**Data category**	**Information**
Primary registry and trial identifying number	ClinicalTrials.gov NCT05159089
Date of registration in primary registry	15 December 2021
Secondary identifying numbers	-
Source(s) of monetary or material support	Col·legi de Fisioterapeutes de Catalunya
Primary sponsor	Col·legi de Fisioterapeutes de Catalunya
Secondary sponsor(s)	n/a
Contact for public queries	[name] ([contact])
Contact for scientific queries	[name] ([contact])
Public title	
Scientific title	
Countries of recruitment	Spain
Health condition(s) or problem(s) studied	Type 2 diabetes mellitus, physical activity adherence
Interventions	Active comparator: Nordic Walking plus the socio-ecological model
	Active comparator: Nordic Walking intervention
	Control comparator: general nurses healthcare follow-up
Key inclusion and exclusion criteria	Ages eligible for study: ≥45 years Sexes eligible for study: both Accepts healthy volunteers: no
	Inclusion criteria: patients with type 2 diabetes
	Exclusion criteria: with contraindications to do physical activity
Study type	Interventional
	Allocation: randomized intervention model. Parallel assignment masking: single blind (evaluator)
	Primary purpose: treatment
	Phase I
Date of first enrolment	14-02-2022
Target sample size	144
Recruitment status	Recruiting
Primary outcome(s)	Physical activity drop-out ratio, physical activity levels, metabolic and health outcomes (HbA1c, blood pressure, waist circumference and BMI) and quality of life.
Key secondary outcomes	Socioeconomic status, social network index and demographic information (sex, gender, age, ethnic origin, marital and family status and medication)

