## Methods/design

### Study design

A mixed methodology will be used. First, a three-arm randomized control trial will compare the effectiveness of a 12-week SENWI programme, a NW programme and typical healthcare advice on PA. The main outcomes will be assessed at baseline, post-intervention and at 9- and 21-month follow-ups. Second, a qualitative thematic analysis using focus groups will aim to understand patient and HCP experiences of the SENWI intervention and factors that may enable or limit patients’ PA drop-out ratio, both of which will be assessed at post-intervention (T1). The study protocol (NCT05159089) was developed based on the Standard Protocol Items: Recommendation for Interventional Trials (SPIRIT) guidelines [43].

An intern Audit Committee will be made up of two research members ([name] and [name]): a specialist in PA research and a statistician. This committee will verify the processes related to recruitment, informed consent, eligibility, assignment to the treatment groups and adherence to the intervention every month. The Committee will meet monthly and will support day-to-day organization of all research teams.

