### Randomization and blinding

A computerized random-number generator (http:// www.randomization.com, created by [name], Tufts University) will be used to randomize eligible participants at the level of the individual participant, stratified by sex and age, in blocks of ten.

Concealed randomization will be conducted by the research member after each participant has been included in the study, has been assigned an identification code and has completed the study baseline assessment. Nurses from CAPs/Hospitals will enrol the participants.

Allocation concealment will be ensured as the random-number generator will not be released until the patient has been recruited into the trial, which takes place after all baseline measurements have been completed. Participants will be notified personally face-to-face.

The design is open label with only outcome assessors being blinded so unblinding will not occur. The researchers carrying out the baseline assessments will be blind to group allocation. The statistician will also be blind to group allocation until the completion of the statistical analysis. Participants will be asked not to reveal group allocation when undergoing follow-up measurements. To assess the extent to which blinding has been preserved, researchers will record the number of cases in which allocation was revealed.

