## Data Availability

All research team members will have access to the trial dataset. Full protocol may be available upon request.

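### As written, the participant code, open dataset access and monthly audit are not compatible with the claimed blinding of assessors and statistician, and no safeguard is stated

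*Protocol article*

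**What the plan says.** Under Randomization and blinding, the protocol article states: "The design is open label with only outcome assessors being blinded so unblinding will not occur". It adds: "The statistician will also be blind to group allocation until the completion of the statistical analysis". The same section says that a research member randomises each participant after an identification code has been assigned and the baseline assessment completed. The registration table is narrower: "Parallel assignment masking: single blind (evaluator"), with no mention of the statistician.

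Four other places bear on this:

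- **Data collection and management.** Confidentiality is protected "using codification (number of participants; number of groups; number of outcome assessments"), and this applies "before, during and after the trial by the principal investigator".
- **Data Availability.** "All research team members will have access to the trial dataset".
- **Study design.** An internal audit committee of two, "a specialist in PA research and a statistician", verifies the processes for "assignment to the treatment groups and adherence to the intervention every month".
- **Nurses' roles.** Study procedure has the nurses select participants for one of the three groups. Patients' intake of medication describes the same nurses as in charge of recruitment and randomisation. Data collection and management has nurses collect everything except the activPAL and qualitative data.

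**The concern.** Participants and instructors know the arm, so blinding of assessors and statistician is the only masking this trial claims. If the arm can be read from a record label, from the shared dataset or from audit material, that protection is lost without anyone noticing. The one planned check records how often allocation was revealed, set beside the request that participants keep it to themselves. It would not pick up unmasking through a code, a file or an audit meeting, so the trial could report an intact blind that was not intact.

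Several steps leave room for influence. Blood pressure is taken manually and waist by tape, the SF-12 is administered by staff, and continued activity is recorded from a participant's answer. The analysis section leaves some choices of method to be made as appropriate.

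**Working it through.** No arithmetic decides this point. It rests on setting the statements side by side.

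1. **Code.** In a list of components of an identifier, the entries most naturally mean a participant number, a group number and an assessment number. A label built this way shows the arm, or at least a constant arm label. It also fits badly with Randomization and blinding, where the identification code exists before randomisation and so cannot contain a group. Either there are two codes or one of the two descriptions is wrong.

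2. **Access.** Quantitative and qualitative outcomes has researchers carry out the assessments. PA assessment has a research team member fit the activPAL. Table 4 lists the research team for the activPAL, the drop-out ratio and the SF-12. The people meant to be blind are therefore within the group that Data Availability admits to the dataset, and no date or exception keeps them out.

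3. **Audit.** Study interventions measures adherence by session attendance. Only the two walking arms have sessions, so anyone who reviews attendance by participant can tell those arms from control. A statistician is on the committee that checks adherence and assignment. If that person also analyses the trial, the claim of a blind statistician fails on this route alone. The article describes no second statistician.

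4. **The outcome itself.** Drop-out during the intervention is a primary outcome, and both Table 4 and PA drop-out ratio define it by attendance. The analyst must receive that variable, and it separates the walking arms from control whatever code or label is used. Full blinding of the statistician is therefore not achievable for this outcome.

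5. **Nurses.** Randomization and blinding gives randomisation to a research member, while two other sections describe nurses as selecting groups or in charge of randomisation. The nurses also collect most outcomes. Read literally, many outcomes are measured by people who know the arm. This is the most direct conflict with assessor blinding, and changing the code, the access rule and the audit would not remove it.

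**The case against.** Each of the first three statements has a harmless reading.

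- The code phrase is loose. It stands in a sentence about confidentiality that also covers potential participants, who have no arm. A group number could be a neutral label whose key the principal investigator holds, and nothing says that assessors see the code.
- The access sentence stands under Data Availability and may mean the final dataset.
- The committee verifies processes, which need not mean participant-level allocation, and its statistician may not be the analyst. Names have been removed, so this cannot be checked.

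The scope for harm is also bounded. activPAL inclusion follows fixed wear-time rules, HbA1c comes from a health-system dataset, and the drop-out answer is registered as yes or no.

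Much of this stands, and it limits the conclusion. A reader might infer that the blinding cannot hold, that the statistician was unblinded in the first month, or that all 144 × 3 = 432 follow-up records display the arm. The document supports none of these. Each needs a particular reading of the code, the access date or the statistician's identity that the text does not fix. Nor does a neutral label fail automatically: someone must both learn a participant's arm and see that participant's code.

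The harmless readings do not remove the point, because none of them is stated. These are rules the article sets out, not details it leaves to a fuller document, and followed as written they undermine a claim it also makes. The attendance and nurse conflicts do not depend on how the code is read.

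**Conclusion.** The concern holds as an incompatibility between stated rules. The code on its natural reading, dataset access without exception, and a statistician's part in the monthly check of assignment and adherence do not fit the blinding claimed under Randomization and blinding, and no safeguard is described. The nurses' stated roles conflict with assessor blinding more directly. The attendance-based outcome makes full blinding of the statistician impossible for that outcome.

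The size and direction of any bias cannot be derived. The conclusion assumes that the code includes a group component and that the access rule applies while the trial runs. The audit route further assumes that the committee's statistician is, or may be, the analyst. If the sponsor can show otherwise on all three, what remains is the nurses' roles and the attendance outcome.

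**What to change.** - **Code.** Build it from the pre-randomisation participant number and the visit number only. Re-label records of those already enrolled (40 at submission) if they carry a group number.
- **Allocation list.** Keep it in a separate file held by the research member who randomises.
- **Access.** Amend Data Availability so that assessors and activPAL processors see neither allocation nor attendance until their data are final.
- **Statistician.** Supply only neutral arm labels until the analysis is complete, as Randomization and blinding promises; release at database lock would be too early. Keep the analysing statistician off the monthly check of assignment and adherence, or drop the claim that this person is blind.
- **Attendance outcome.** State that the statistician cannot be fully blind for it. Analyse the other outcomes before the attendance file is released.
- **Nurses.** Reconcile Study procedure, Patients' intake of medication, and Data collection and management with Randomization and blinding, or limit the assessor-blinding claim to the outcomes for which it is true.

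The cost is mainly protocol wording, a split of files, re-labelling of at most the records already collected, and a fixed order of analysis. Taking the analysing statistician off the audit means giving that check to someone else. Separating the nurses who allocate from those who measure could need staff time; narrowing the claim would not.

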### Data analysis

Descriptive statistics will be reported as the mean and standard deviation (SD) for quantitative variables (PA and metabolic and health assessment outcomes) and using frequency rates and percentages for qualitative variables (drop-out ratio, medication, quality of life, socioeconomic status and social network). The Shapiro–Wilk test will be used to assess the normality of quantitative variables. For each outcome variable considered, the effect of the three different interventions will be assessed by a two-factor analysis of variance: the first factor will be the treatment group and the second factor will be time. To determine whether one treatment improves the scores of the study variables compared with the other, two-factor ANOVA tests will be performed with linear mixed models for repeated measures. An odds ratio and hazard ratio will be performed comparing drop outs in SENWI, NW and the control group at 3, 9 and 21 months.

Socioeconomic status and social network index will be analysed and compared in relation to the PA attendance at 3, 9 and 21 months post-intervention using the non-parametric chi-square test (*χ*^2^) and logistic regression when appropriate.

Demographic and other patient characteristics recorded (e.g. age, gender, marital status, income, education and employment) will be tabulated and analysed as covariables alongside the PA levels and PA drop-out ratio at the beginning and at 21 months post-intervention. Correlations and differences between groups and these variables will be analysed. Difference in baseline levels of outcome variables (PA, drop out, HbA1c and so forth) will be identified, and the correlation with the different covariables will be assessed.

A *p*-value of < 0.05 will be considered statistically significant. When multiple comparisons are carried out, the Bonferroni correction will be applied. All analyses will be carried out with the obtained data without employing missing data replacement techniques. Analysis will follow intention-to-treat principles. Assumptions will be tested regarding missing data, randomization and contamination. All analyses will be carried out using the R version 3.6.1 software.

The individual intervention will be regarded as successful if (i) it leads to an average increase in activity and (ii) the participant did not drop out of the PA (NW or any kind of PA) in the long run (i.e. if the patients answer yes when asked if they still do PA of some kind).

The SENWI programme will be regarded as improving usual healthcare if it increases PA at any level [2]. We will assess changes between groups in indicators relating to people living with T2DM health issues including HbA1c, weight, waist circumference and blood pressure. Finally, comparison between groups variables at 9 and 21 months will be needed to see whether the SENWI protocol is effective or not, and to determine if the PA drop-out ratio increases after removing the social and economic support (i.e. study intervention), in relation to the NW and SENWI.

To establish how the intervention works and for whom moderator and mediator analysis will be conducted. Suspected moderators will include participants’ demographic factors (e.g. socioeconomic status) and baseline intentions to engage in activity (e.g. sociocultural needs).

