### Participants

A total of 144 participants (randomized in two intervention groups and one control group) will be included in this study. The study will be conducted in the Central Catalonia health area (Spain). Participants will be recruited from Monistrol de Montserrat *Primary Care Center* (CAP), Vic Sud CAP (Vic), CAP les Bases (Manresa), Hospital *Sant Bernabé* (Berga) and Anoia CAP (Igualada).

Inclusion criteria for eligibility will include participants (i) with T2DM, (ii) that have no major physical limitations prescribed by the doctor or any HCP and (iii) that are physically inactive according to the Spanish version of a Brief Physical Activity Assessment Tool – SBPAAT screening tool [44]. Participants will be excluded if they (i) are pregnant or have T2DM due to gestation; (ii) are unable to freely consent to take part in the study; (iii) are unable to understand the study materials or PA intervention; (iv) have complications such as neuropathy, retinopathy and nephropathy; (v) have relative or absolute contraindications to do PA; and (vi) have a body mass index over 34.9 kg/m^2^ since Nordic walking uses poles that require free arm mobility that is impaired by a body mass index over 35 kg/m^2^.

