### Sample size

We calculated the sample size (*n* = 144) in relation to the drop-out ratio in PA interventions showed by other studies (15%) [45] with a balanced one-way analysis of variance power calculation of 80%, a significance level of 5%, an expected drop-out rate in participants of 15% and an effect size of 0.5. As a result, 48 participants will be needed in each group in the three-arm randomized controlled trial.

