### Study interventions

A three-arm randomized controlled trial will assess the impact of a primary care-based PA intervention implementing SENWI against an isolated NW programme (comparison group 1) (see Fig. 1) and usual PA advice (e.g. to walk) provided by HCPs (comparison group 2).

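### Bonferroni is a valid but needlessly conservative correction for a three-arm comparison; Holm, or a global test followed by pairwise tests, would keep the same 5% familywise error with more power (optional gain)

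*Protocol article*

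**What the plan says.** The Data analysis section sets the threshold (a p-"value of < 0.05 will be considered statistically significant") and then the correction: "When multiple comparisons are carried out, the Bonferroni correction will be applied". It does not say whether the comparisons meant are pairs of arms, time points, outcomes or some combination.

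The same section plans a global comparison for each outcome: "the effect of the three different interventions will be assessed by a two-factor analysis of variance", with treatment group and time as the factors, carried out with linear mixed models for repeated measures.

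There are exactly three arms: "A total of 144 participants (randomized in two intervention groups and one control group) will be included in this study". Under Study interventions the socio-ecological programme is set against each of two comparators, NW and usual advice. For the first: "A three-arm randomized controlled trial will assess the impact of a primary care-based PA intervention implementing SENWI against an isolated NW programme".

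The Sample size section gives "an expected drop-out rate in participants of 15% and an effect size of 0.5", with 80% power and a 5% level in a one-way analysis of variance, and concludes that "48 participants will be needed in each group in the three-arm randomized controlled trial". It does not say what kind of effect size 0.5 is.

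**The concern.** Applied to three pairs of arms, Bonferroni tests each pair at 0.05/3 = 0.0167. With three groups that is stricter than a 5% familywise error requires, because the pairwise hypotheses are logically linked: if any one pair differs, at most one of the three equalities can still be true. A rule that uses this link can test pairs at a higher level with the same familywise guarantee.

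What is at stake is power, mainly for SENWI against NW, the contrast that isolates the socio-ecological component. The arms are small, so the choice of correction can matter. Type I error is not at risk under the current rule.

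**Working it through.** **Inputs.** 48 per arm and 15% drop-out (Sample size): 48 × 0.85 = 40.8, taken as 41. Significance level 0.05 (Data analysis), taken as two-sided because sidedness is not stated. Effect 0.5 (Sample size), read as a difference of 0.5 SD: an assumption. The control mean relative to NW is not given and is varied.

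**The plan's own figure.** 48 per group does not reproduce from the stated inputs. With 0.5 as Cohen's f, three groups need 14 each (17 with drop-out). With 0.5 as a standardised difference between two arms, two-sided 5%, 63 are needed (75 with drop-out). That is a separate matter; the calculations below take the stated 48, less drop-out, as given.

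**Why two steps suffice.** Write the null hypotheses as S = N, S = C and N = C. Any two of them together imply that all three arms are equal. The closed family therefore has only four members: the global null and the three pairs. By the closure principle, a pair may be declared different if the 2-df global test and that pair's own test are both significant at 5%. If the global null is true, a false claim requires a false global rejection (at most 5%). If it is false, at most one pair null is true, and it is tested once at 5%.

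**Power under Bonferroni (exact).** Pooled SD, df = 3 × 41 − 3 = 120. Noncentrality = 0.5/√(2/41) = 2.264.
- Three pairs, level 0.0167: critical t 2.428, power 43.8%.
- Two SENWI contrasts only, level 0.025: critical t 2.270, power 50.0%.
- Uncorrected, level 0.05: critical t 1.980, power 61.3%. With a single normal outcome, this is the ceiling for any rule that tests the pair at no more than 5%.

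**Simulation (400,000 normal-outcome trials per scenario, 41 per arm). Power for SENWI against NW:**

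| Control mean | Bonferroni, 3 pairs | Holm, 3 pairs | Global test, then pairs | Gain of two-step over Bonferroni |
|---|---|---|---|---|
| Equal to NW | 44% | 46.5% | 54% | about 10 points |
| Midway between NW and SENWI | 44% | 45% | 48% | about 4 to 5 points |
| 0.5 SD below NW | 44% | 56% | 61% | about 17 points |

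With NW equal to control and the full 48 per arm, the figures are 51% (Bonferroni) and 62% (two-step).

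**If 0.5 is Cohen's f.** With NW equal to control, the SENWI difference is 0.5 × 3/√2 = 1.06 SD. Power is then about 99% under Bonferroni, and the gain is 0.6 points at 41 per arm. With equally spaced means in the order SENWI, NW, control, the gain is about 15 points at 41 per arm (64% to 79%).

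**If the family is only the two SENWI contrasts.** With NW equal to control, Bonferroni at 0.025 gives 50% and Holm over the two gives 55%. The two-step rule's 54% is then about 4 points above Bonferroni and no better than Holm.

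**Familywise error.** Two-step rule: 5.0% under the global null and at most 5.0% with one arm different, within simulation error. Bonferroni over three pairs: about 4.4% and 1.7%.

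**The case against.** The strongest reply is that nothing here is wrong: Bonferroni is valid, stated in advance and consistent with the rest of the section. That stands. A reader might infer from the power figures that the plan contains an error; the documents do not support that.

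The family of three pairs at 0.0167 is also a reading, since the section defines no family. This stands too, and it matters: if only the two SENWI contrasts are corrected for, more than half of the 10-point gain disappears.

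A reader might take 10 points as a fixed figure. It holds only if 0.5 is a standardised difference and NW equals control, and the document states neither.

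A reader might also say that Bonferroni buys no extra protection. It does: with one arm different its error is about 1.7% against 5%, and it comes with matching simultaneous intervals. The defensible claim is that this exceeds the 5% target.

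Nor do the documents require SENWI to beat both comparators. The Discussion of the abstract and the Conclusions mention both, but the success statement in Data analysis concerns improving on usual care. If both wins were required, each contrast could be tested at 5% with no correction at all.

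Finally, testing pairs at a full 5% for every outcome and time point would be unsafe as a complete rule. Seven primary measures (drop-out, activity, HbA1c, blood pressure, waist, BMI, SF-12) at up to three later times give up to 21 analyses. If these were independent with no true effects, the chance of at least one false claim would be about 1 − 0.95^21 = 66%. The current sentence, read broadly, covers those comparisons, so a replacement must not drop that cover.

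The simulation is for a single normal outcome. The closure argument carries over to a 2-df contrast in a mixed or logistic model, but these power figures do not transfer directly to repeated measures or to binary drop-out.

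**Conclusion.** The point holds as an optional efficiency improvement. For three arm pairs within one outcome and time point, a global test followed by pairwise tests keeps the 5% familywise error and raises power for SENWI against NW from about 44% to 54% at 41 per arm, if 0.5 is a standardised difference and NW equals control. On the same reading of 0.5 the gain runs from about 4 to 5 points to about 17, depending on the control mean. It is near zero for very large effects and about 4 points if the comparison is with Bonferroni over the two SENWI contrasts. Holm needs no assumption beyond those of Bonferroni and never rejects less, but in the base case it gains only about 3 points. The plan's error control is sound as written.

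**What to change.** Name the family, and replace the Bonferroni sentence with something like:

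*Where a family of hypotheses is corrected for multiplicity, Holm's procedure is used. For the three pairwise arm comparisons of one outcome at one time point, the 2-df contrast of no arm difference for that outcome and time point, from the planned model, is tested first at the level allotted to it. Only if it is significant is each pair tested, at that same level. This step controls error within that outcome and time point only and does not replace any correction across outcomes or times.*

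The level allotted to each outcome and time point should be fixed in advance. Raising it by Holm across outcomes after a global rejection is not automatically covered, because one pair null in the rejected outcome may still be true. With two outcomes the bound would be 2.5% + 5% = 7.5%.

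The cost is a short change of text before analysis, with no extra participants or measurements. The downsides are that the pairwise 95% intervals are no longer simultaneous, and that the error rate with one arm different rises from about 1.7% to the nominal 5%.
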